### The intervention

The interventions utilised in ASPIRE will focus on health-improving lifestyle activities to achieve outcomes related to weight loss, increased employability and general improvement in health and quality of life. In order to improve acceptability and enhance participation, interventions will be tailored to meet the different needs of participants who are likely to be at different stages of their weight loss or employability journey. Interventions will be co-designed with participants to ensure ownership of the model and will be adapted by the different implementation sites to suit their capacity, resources and potential participants. The ASPIRE model will consist of three interconnected elements and a fourth element which links the different elements together. The three elements include the following: (1) being active (grow your own), (2) healthy food and nutrition (eat your own), (3) achieving personal goals and improving employability (sell your own). The fourth element will be improving self-esteem through enhancing wellbeing, community engagement and accountability. It is important to note that the ASPIRE model uses a holistic approach and therefore all the elements are linked to each other via the core outcome of increasing self-esteem and support within the community. Table 1 outlines the different elements and details of interventions under each element. Activities will be delivered by trained professionals, experienced volunteers or partner agencies with experience in nutrition, health, wellbeing and employability.

**Table 1 Tab1:** Overview of the core elements of the ASPIRE model and intervention activities

ASPIRE theme	Intervention activities
Self-esteem and support within a community	• Virtual reality guided meditation • Listening points • Self-care and self-image support activities • Motivational interviewing • Sophrology • Positive experience workshops • Integration into a commitment valuation system • Understanding behaviour change workshops
Grow your own - ‘Being Active’	• Setting up and maintaining community allotment or personal vegetable patch workshops • Walking groups • Understanding of seasonal and local food cultivation workshops • Fitness and wellbeing classes: yoga, tai chi, mindfulness • Health and safety in the garden workshop • Level 1 Award in Horticultural Skills
Eat your own - ‘Nutrition’	• Diet and nutrition workshops • Cooking classes • Food shop on a budget tools and support • Cooking on a budget/cooking with leftovers resources • Sourcing cheaper healthy produce • Meal planning, reducing waste and food preservation workshops. • Cooking with home grown produce • Cooking with limited resources • Food Safety in Catering Levels 1 and 2 • Level 1 Cert in Food prep and cooking
Sell your own - ‘Achieving goals and employability’	• Soft skills recognition and development workshops • Links with local business to offer volunteering and work experience • Interview preparation: mental and physical via workshops and virtual reality • Entrepreneurship support • Workshops to define skills (interpersonal skills and know-how), strengths and weaknesses • Know how to introduce yourself (in connection with the virtual reality interviews) • Interview with a referent • Level 2 Principles of COSHH (Control of Substances, Hazardous to health) • Level 2 Principles of Manual Handling • Level 3 Emergency First Aid at Work.

### Data collection

Consistent with realist principles and methodology, a mixed-method approach will be used for data collection. This will involve collecting both quantitative and qualitative data to refine the final programme theory on what aspects of the interventions in ASPIRE work, for which participants and in what context. The quantitative assessments will be used to objectively measure the outcomes which occur as a result of the intervention and qualitative assessments will provide more insights into why the interventions were effective or failed to achieve the desired outcome. Using a one-group pre-post methodology, participants will be followed up over time and data will be collected at four time points T0 (at the beginning of ASPIRE), T1 (at 12 weeks), T2 (at 6 months) and T3 (at 9 months) to map participants’ journey through the programme. At baseline (T0), the intervention will be explained to the potential participant and the consent will be obtained from the participant. This will be followed by administration of baseline questionnaires and measurement of baseline anthropometrics. All questionnaires used for data collection will be available in both French and English to ensure that no participants are excluded on the basis of language. Evaluation materials will be piloted to ensure consistency, comprehension, clarity of questions and coherence of both English and French versions and appropriate modifications will be made. A standard operating procedure for data collection has been developed and training on the evaluation and data collection process will be provided to project coordinators at the ASPIRE hubs to ensure accuracy and adherence to international standards for assessing anthropometry.

### Demographic data

Data on socio-demographic characteristics including age, gender, level of education and duration of unemployment will be collected using questionnaires.

### Primary outcomes

#### Weight, height, body mass index and body fat percentage

Weight, height, BMI and body fat percentage will be measured using the Interactive Health Kiosk (Model Number: SLF007 – Wellbeing People, Marden, Kent, England). The weighing platform of the Health Kiosk is based on load cell technology with a maximum capacity of 180 kg. Body fat percentage will be measured using multiple frequency bioimpedance analysis (BIA) technology. Weight and body fat percentage will be measured without shoes or heavy clothing to the nearest 0.1 kg and 0.1%, respectively. Height will be measured using a stadiometer (Model number: Seca 213, Seca UK) according to standard procedure for measuring height to the nearest 0.1 cm. BMI will be calculated as weight in kilograms divided by height in metres squared.

#### Employment status

Employment status will be assessed by partners at local ASPIRE hubs by detailing when a participant obtains remunerated work (full-time and part-time) or subsidised work. In the analyses, employment status will be coded as a dichotomous variable (employment versus no employment) and no distinction will be made between the different types of employment. The ASPIRE participation ladder (Fig. 2) will also be used to further document participants’ status on the ladder when they join the intervention and throughout their journey to map out their rise on each stage of the ladder. The ladder consists of a series of 5 steps linked to activities and outputs to map participants’ progress through ASPIRE. The steps are as follows: ‘Join an ASPIRE hub’, ‘Regularly attend hub’, ‘Begin employment training’, ‘Volunteer/work experience’ and ‘Paid employment’.

**Fig. 2 Fig2:**
[figure not shown]
ASPIRE Participation/employability ladder. The ASPIRE participation/employability ladder describes the series of steps, activities and outputs to map participants’ progress through ASPIRE. **Abbreviations**: ASPIRE, Adding to Social capital and individual Potential In disadvantaged REgions

### Secondary outcomes

#### Dietary intake and diet quality

A validated semi-quantitative food frequency questionnaire (FFQ), which includes 183 food items and a section with open questions will be used to collect data on dietary intake and diet quality. This instrument is an adapted version of the Metacardis [34] and EPIC FFQs [35, 36] to reflect the general diet in France and England and is suitable for use in both countries. Using standard portion sizes, the FFQ measures an individual’s habitual food and nutrient intake during the past year. Validation studies have shown the instrument to accurately estimate dietary intake with significant correlations with biomarkers and other dietary assessment methods.

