**Methods:**

A mixed-method realist evaluation using a single-group before-and-after design will be used. The evaluation will consist of development of an initial programme theory, theory validation and refinement using quantitative and qualitative data to understand the causal mechanisms, contexts of implementation and their interactions that result in outcomes observed in ASPIRE. Primary outcomes that will be assessed are change in body weight and body mass index, reemployment and a rise on the ASPIRE participation ladder. The ASPIRE participation ladders consists of a series of 5 steps to engage participants in the project. The first step on the ladder is joining an ASPIRE hub with paid employment as the final step on the ladder. Secondary outcomes will be physical activity, diet quality, self-efficacy and health-related quality of life. Both quantitative and qualitative approaches are appropriate in this study because the use of validated questionnaires and objective measures will demonstrate how much the intervention addressed outcomes related to weight loss and reemployment and the qualitative data (photovoice) will provide insights into the contexts and experiences that are unique to participants in the project.

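### The food frequency questionnaire looks back one year but the last visit is at 9 months, so any follow-up diet score includes pre-programme diet

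*Protocol article*

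**What the plan says.** Under Dietary intake and diet quality, the Protocol article describes a validated, semi-quantitative FFQ with 183 items, adapted from two existing instruments, which "will be used to collect data on dietary intake and diet quality". It says that the instrument measures "habitual food and nutrient intake during the past year". It gives no different period for follow-up.

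Under Data collection it states the design and schedule: "Using a one-group pre-post methodology, participants will be followed up over time", and "data will be collected at four time points". These are T0 at the start of ASPIRE, T1 at 12 weeks, T2 at 6 months and T3 at 9 months. There is no timetable by instrument. The same section says the evaluation materials will be piloted and modified where needed.

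The abstract gives the outcome its rank: "Secondary outcomes will be physical activity, diet quality, self-efficacy and health-related quality of life".

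**The concern.** A before-and-after comparison needs the follow-up measurement to describe the period after the start. With a one-year look-back and a last visit at 9 months, no follow-up FFQ can describe programme time alone. If participants answer as instructed, each follow-up score is a mixture of diet before and during the programme, and the difference from T0 understates a sustained change.

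The mixture also changes from visit to visit. A diet improvement that is immediate and then constant would look like steady growth from T1 to T3, and one that fades could look maintained. The schedule is meant to follow participants' progress through the programme, and there is no control group against which to judge the pattern.

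Healthy food and nutrition is one of the three core elements listed under The intervention, so a misleading diet result could feed into the refinement of the programme theory. The other self-report instruments whose recall period is stated fit the schedule: one week for physical activity and 30 days for physical health.

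**Working it through.** **Inputs.** Recall window: one year, taken as 52 weeks or 12 months (Dietary intake and diet quality). Visits: 12 weeks, 6 months and 9 months after T0 (Data collection). The document gives no diet effect, diet standard deviation or diet sample size, so there is no diet figure to reproduce. Its only computed size, 871, is for weight change. A paired t-test with effect size 0.11, 90% power and two-sided α = 0.05 reproduces it, and it plays no part below.

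**Step 1: share of the window before the programme.** Share = 1 − (time since T0) / (window).
- T1: 1 − 12/52 = 40/52 = 76.9%
- T2: 1 − 6/12 = 50%
- T3: 1 − 9/12 = 25%

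This step needs no assumption about recall or effect. The T1 and T2 values apply only if the FFQ is given at those visits.

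**Step 2: share of a true change that the FFQ would show.** This does need assumptions, so a range is given. Let m be months since T0 (12 weeks = 12/52 × 12 = 2.77 months) and f = m/12.
- Step change at T0, all weeks weighted equally: f.
- Linear ramp from zero at T0 to the level reached at the visit, equal weights, as a share of the change present at the visit: f/2.
- Step change at T0 with recall weights that halve every h months going back (h is assumed): (1 − 2^(−m/h)) / (1 − 2^(−12/h)).

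| Scenario | T1 | T2 | T3 |
|---|---|---|---|
| Step change, equal weights | 23% | 50% | 75% |
| Step change, recency-weighted, h = 6 months | 36.5% | 67% | 86% |
| Step change, recency-weighted, h = 3 months | 50% | 80% | 93% |
| Linear ramp, equal weights | 12% | 25% | 38% |

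For example, with h = 6 at T2: (1 − 0.5) / (1 − 0.25) = 0.667. Every entry is below 100%, and in every row the share rises from T1 to T3.

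**Step 3: effect on the time course, equal weights.** A constant improvement from T0 reads 23%, 50%, 75%, which looks like growth. An improvement that lasts exactly 12 weeks and then disappears stays inside the one-year window at all three visits and reads 12/52 = 23% each time, so complete relapse looks like maintenance.

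**Step 4: a window that fits.** A window no longer than the T0–T1 interval of 12 weeks has a pre-programme share of 0% at T1, T2 and T3. Three calendar months is slightly too long: about 13 weeks, leaving (13 − 12)/13, or about 8%, before the programme at T1.

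**The case against.** **FFQ timing is inferred.** The schedule is general. The article mentions a standard operating procedure and supplementary material, neither shown, which could set other timing or wording for a long questionnaire. This stands as a limit on the T1 and T2 figures. It does not remove the point: even a single follow-up FFQ at 9 months reaches back three months before T0.

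**Size and net direction are uncertain.** This also stands. The 23/50/75% row is one scenario among several. In an uncontrolled design, social desirability or similar reporting error could push the measured change upwards. Attenuation is the expected effect of the window, not a proven net bias.

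**Sample size.** A reader might go on to infer that the sample needed for diet rises with the inverse square of the retained share. The documents do not support that. It would require the standard deviation of change to stay the same, although overlapping windows should also reduce it, and no diet sample size is stated.

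**Importance.** A reader might also infer that diet is a key mechanism of the realist model. The text does not say so. The Discussion names engagement and participation as the hypothesised mediators, and the conceptual framework figure is not shown. Paired t-tests and repeated-measures analysis are named only for weight and BMI.

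**The remedy trades one problem for another.** A one-year window largely averages out season. With 12 weeks, T0 and T2 fall in opposite seasons, in a programme built on growing food. If enrolment clusters in one season, season and time since T0 may not be separable. This is a real cost, but it can be recorded and examined, and it does not make a one-year look-back suitable at 12 weeks.

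**Conclusion.** The point holds as a mismatch between two things the article states, not as a missing detail. The recall window exceeds every follow-up interval. The overlap with pre-programme time is certain for any follow-up use of the FFQ as described: 25% at T3, rising to 50% at T2 and 77% at T1 if the questionnaire is given at every visit, which is the natural reading.

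A sustained diet change would be expected to be attenuated. Across the scenarios examined, the share shown runs from 12% to 50% at T1, 25% to 80% at T2 and 38% to 93% at T3. These ranges rest on assumed recall weights and an assumed course of change, and on no other reporting error. The distortion of the time course follows from the same unequal dilution.

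One secondary outcome is affected. Weight, BMI, employment and the participation ladder are not. The change is worth making because it is cheap, not because the evaluation fails without it.

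**What to change.** During the planned piloting, set one reference period no longer than the T0–T1 interval, worded as the past 12 weeks rather than three months, and use it at T0 and at every follow-up FFQ. State at which visits the FFQ is given. Record the date of completion and account for season in the diet analysis.

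The cost is a change of instruction wording in a questionnaire that is already adapted, in both languages. There are two downsides to declare: the stated validation may not carry over to the shorter window, and a 12-week window is more seasonal than a one-year window.

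The trial was registered retrospectively, so some baselines may already exist. If they were collected with the one-year window, changing it now would break comparability with T0. In that case keep the window, do not interpret T1 or T2 FFQ scores as programme-period change, and report the T3 change as diluted, with about a quarter of its window before the programme. This alternative costs only a statement on interpretation.

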#### Self-efficacy

This will be assessed using The General Self-Efficacy Scale (GSE) [37]. This is a 10-item self-administered scale which assesses a general sense of perceived self-efficacy with the aim of predicting how individuals cope with daily challenges and adaptation after experiencing all kinds of stressful life events. Responses are based on a 4-point scale and the sum up of responses to all 10 items yield a final composite score ranging from 10 to 40 with a higher score indicating more self-efficacy. The scale has been validated for use in general adult populations, and in samples from 23 different countries, Cronbach’s alpha ranged from 0.76 to 0.90 indicating high reliability. The GSE has been shown to positively correlate with emotion, optimism, work satisfaction. Negative coefficients were found for depression, stress, health complaints, burnout, and anxiety [38].

#### Health-related quality of life

The five-level EuroQol EQ-5D-5L questionnaire [39] will be used to assess this outcome. This instrument consists of a short descriptive system questionnaire and a visual analogue scale (EQ VAS) and provides a simple descriptive profile of a respondent’s health state. The instrument is one of the most widely used globally for measuring health status and has been proven to be valid, reliable and sensitive in varied populations [39–41].

#### Physical activity

Physical activity will be measured using self-reported assessments of physical activity on a 2-item questionnaire which reports participants’ engagement in light, moderate or vigorous physical activity over the previous week as well as the duration and frequency of the activity.

#### Health, wellbeing and activity

Self-reported health status will be assessed using 5-items on the health, wellbeing and activity questionnaire consisting of questions asking participants to rate their physical health over the past 30 days.

#### Workability

This will be assessed using 4-items adapted from the work ability and functional capacity self-assessment questionnaire [42].

### Qualitative data

Qualitative data will be obtained from participants using Photovoice. Photovoice is a community-based participatory research (CBPR) technique whereby participants identify, represent, and enhance their community through photographs and narratives [43]. As a methodology, photovoice has been used extensively in research to explore wellbeing and enabled participants to identify activities and places that enhanced their wellbeing [44]. It has also been used in studies on unemployment and food insecurity [45], and as a useful tool to engage with disadvantaged groups [46]. The technique has been shown to act as a catalyst, bringing impacts ranging from an increased sense of accomplishment to a deeper understanding of the reality of participants’ daily lives [46]. Using participatory visual methods will enable the participants to be creators of their own stories. Participants will be able to exercise control over the presentation of themselves, their wellbeing and their employability aspirations through the process, and using visual images such as photographs can empower participants to recognise their autonomy [47]. Within the ASPIRE project, a subset of participants purposively sampled will be encouraged to take up to 6 images of what the project means to their wellbeing and/or employability over 7 consecutive days and also complete a logbook documenting each photograph. These photos will be further discussed in a semi-structured interview to obtain insights into participants’ experience of ASPIRE and impact of the project on their wellbeing and employability. All interviews will be recorded on a digital Dictaphone for the purpose of transcription.

### Data analysis

Statistical analysis of quantitative data will be conducted using Statistical Package for Social Sciences (SPSS) IBM statistics (version 26, SPSS UK Ltd. Chertsey, UK). The normality of continuous variables will be checked using QQ-plots and the Shapiro-Wilk test. All tests will be carried out at the 95% confidence interval and in all analyses, a threshold of *p* < 0.05 will be considered statistically significant. Chi-square tests for independence will be used for comparing categorical variables such as sex and employment status. Means and standard deviations will be computed for continuous variables including age, body weight and BMI. Paired t-tests and repeated measures analysis will be used to examine the effect of the intervention on body weight and BMI of participants over time. Correlations and regressions or non-parametric equivalents as appropriate will be used to examine the relationships between continuous variables. The contribution of demographic variables to predicting BMI and behaviour change will be assessed using multiple linear regressions. The analysis will be conducted using intention-to-treat principles and for completers only.

Qualitative data (photos and transcript form semi-quantitative interview) will be analysed using NVivo Pro 12.5 (QSR International, 2020), which permits the coding of photos as well as text. Interviews will be audio recorded with the participants’ consent and transcribed. Thematic analysis and content analyses using both deductive and inductive approaches [48] will be used to test initial theories while allowing for emergence of new themes, and will include stages of familiarisation, coding, indexing and charting, mapping and interpretation. The deductive analysis will enable to test whether data are consistent with prior assumptions and theories identified during the development of the initial programme theory. The inductive approach which is guided by specific evaluation objectives will allow research findings to emerge from the frequent, dominant, or significant themes inherent in the raw data.

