#### Participants

Participants for the study will be recruited from communities within the 7 ASPIRE implementation sites. Recruitment will be carried out at community and unemployment centres, via flyers, online posts, posters and referrals from general practitioners, weight management clinics and social prescribing. Participants are eligible if they meet the inclusion criteria. Inclusion criteria will be adults (18 years above) who are unemployed, jobseekers or living with overweight or obesity (BMI between 24 kg/m^2^ and 40 kg/m^2^) using WHO classification [32] and ability to participate in activities. A lower BMI cut-off of 24 kg/m^2^ was chosen to include individuals at risk of becoming overweight and to capture participants with the risk of developing other chronic diseases. Exclusion criteria will be as follows: terminal illness or palliative care, dementia, a severe mental health problem or learning difficulty; serious health conditions that will affect uptake of intervention activities; planned bariatric or weight loss surgery; serious psychosocial problems or behavioural problems that could hinder participation in interventions (e.g. drug addiction, serious psychiatric disorders, aggressive delinquent behaviour); pregnant or planning to become pregnant and individuals currently involved in full-time paid employment or recurrent short-term contracts. Individuals who do not meet the eligibility criteria because of serious health conditions will be referred to local general practitioners or the appropriate health service provider. Ethical approval has been obtained in line with the Bournemouth University Research Ethics Committee Code of Practice (Ethics ID: 33136). Informed consent will be obtained from participants prior to enrolment in the intervention. Participants who respond to the study invitation will receive a participant information sheet with detailed information concerning the project, the nature and objectives of the study and possible risks associated with their participation and will be required to sign a consent form before participating in activities at the ASPIRE hub. All data collected for this project will be anonymised and no identifying characteristics of respondents will appear in final manuscripts, reports and publications.

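### Reemployment and a ladder rise start at or near a floor in an uncontrolled before-after design, so background job-finding or ordinary attendance would register as improvement

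*Protocol article*

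**What the plan says.** All references are to the protocol article.

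- **Design.** Abstract, Methods: "A mixed-method realist evaluation using a single-group before-and-after design will be used". The Data collection section repeats it ("Using a one-group pre-post methodology"). There is no comparison group, and the Abstract and Methods give effectiveness as an aim.
- **Outcomes.** Abstract, Methods: "Primary outcomes that will be assessed are change in body weight and body mass index, reemployment and a rise on the ASPIRE participation ladder".
- **Who enters.** Participants section: "Inclusion criteria will be adults (18 years above) who are unemployed, jobseekers or living with overweight or obesity". Among those excluded are "individuals currently involved in full-time paid employment or recurrent short-term contracts". Part-time work is not named as an exclusion.
- **What counts as employment.** The Employment status section has the hubs record it "by detailing when a participant obtains remunerated work (full-time and part-time) or subsidised work", coded as a yes/no variable.
- **The ladder.** "The first step on the ladder is joining an ASPIRE hub with paid employment as the final step on the ladder". The Employment status section lists five steps, of which the second is attending the hub regularly. Each participant's step is recorded at joining and afterwards.
- **Tests.** Data analysis section: "Chi-square tests for independence will be used for comparing categorical variables such as sex and employment status". Weight and BMI get paired t-tests and repeated-measures analysis. No test is named for the ladder. The 0.05 threshold applies to every analysis.

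**The concern.** A before-after comparison without controls shows an effect only if the outcome would otherwise have stayed put. Employment among people recruited largely because they lack work will not stay put: some find a job within nine months whatever the programme does. The ladder has the same problem built in. A person who starts at step 1 can only stay or rise, and coming to the hub regularly is already a rise. Its last step is paid employment, so a person who finds work can score on two primary outcomes through one event.

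The named test adds a second, smaller problem. A chi-square test for independence asks whether two classifications are associated. Applied to the same people before and after, it does not ask whether the proportion in work has changed.

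At stake is a claim of effectiveness on two of the four listed primary outcomes. The Discussion intends the findings to inform policy and to be embedded in services.

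**Working it through.** **Inputs.** From Sample size: minimum 871, effect size 0.11, power 90%, alpha 0.05, 15% added for clustering, 30% attrition, total 1303. From Data collection: last follow-up at 9 months. The documents give no employment rate at T0 and no rate of finding or losing work, so those below are assumptions.

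**The plan's own figures.** A two-sided paired t-test with d = 0.11 and n = 871 has power 0.9002, so 871 reproduces. 871 × 1.15 = 1001.65, rounded up to 1002; 1002 × 1.30 = 1302.6, rounded up to 1303. With 30% of 1303 lost, 1303 × 0.70 = 912 are followed up. No sample size or expected rate is given for reemployment or the ladder.

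**How few job-finders reach p < 0.05 if nobody works at T0 (n = 912)**

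- Chi-square, before and after treated as independent groups, 0/912 against 4/912: 1824 × 4 / 1820 = 4.01, p = 0.045. Four people, 4/912 = 0.44%. With continuity correction six are needed (p = 0.041), as with Fisher's exact test (p = 0.031).
- Exact McNemar, k entering work and none leaving: p = 2 × 0.5^k. For k = 5, p = 0.0625; for k = 6, p = 0.031. Six people, 6/912 = 0.66%.
- The counts of four and six are the same at n = 871 and n = 1303.

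**Chance of p < 0.05 with no programme effect.** The number finding work is binomial (912, r), with r the assumed background rate over 9 months.

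| r | Chi-square (4 or more) | Exact McNemar (6 or more) |
|---|---|---|
| 0.5% | 67% | 31% |
| 1% | 98% | 89% |
| 2% | >99.9% | >99.9% |
| 5% to 30% | about 100% | about 100% |

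**If some start in part-time work.** The floor weakens. Chance of a significant rise over 4,000 simulated trials, using the uncorrected large-sample form of each test:

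| Employed at T0 | Find work | Lose work | Chi-square | McNemar |
|---|---|---|---|---|
| 5% | 5% | 30% | 89% | 98% |
| 20% | 20% | 10% | about 100% | about 100% |
| 20% | 10% | 30% | 8% | 37% |
| 20% | 5% | 30% | 0% | 0% |

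**Whether a test for independence measures change.** Suppose 46 of 912 work at T0, 10 leave work and 10 enter it. The T0-by-follow-up table is 36, 10 / 10, 856, with zero net change. Chi-square = 912 × (36 × 856 − 10 × 10)² / (46 × 866 × 46 × 866) = 912 × (30716/39836)² = 542, p below 1e-100. McNemar on 10 against 10 gives p = 1.0. If nobody works at T0, one row of this table is empty and the statistic cannot be computed.

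**The case against.** The strongest reply is that the chi-square sentence is generic. It names sex, which does not change between visits, and the Final Programme theory section plans comparisons by sex, site location and duration of unemployment. Chi-square suits those comparisons. The same Data analysis paragraph keeps its wording about intervention effects over time for weight and BMI, with paired methods. On that reading employment has no named before-after test, and a condensed article may leave that to a fuller plan. This stands: a reader might infer that chi-square is the declared before-after test, but the text does not say so.

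Three other inferences also go too far.

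- *That the ladder is given a chi-square test.* It is not mentioned in Data analysis.
- *That eligibility puts everyone at ladder step 1.* The ladder's floor is its own first step. Status at joining is recorded, so some may start higher.
- *That the two outcomes cannot fail.* The word or in the inclusion criteria lets in people with overweight who are not unemployed. Part-time work is not excluded yet counts as employment, so employment can fall. The last two rows of the second table show that a significant rise is then far from certain.

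It is also fair that a single-group design is openly declared, that the overlap between step 5 and reemployment is visible, and that the protocol nowhere calls them independent evidence.

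None of this removes the core. Outcomes, ladder steps, design, effectiveness aim and significance threshold are all fixed in this document, and no later choice of test supplies a comparator.

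**Conclusion.** The point holds in a limited form. Reemployment and a ladder rise can hardly fall when most participants start without work and at the bottom of the ladder. With no comparator or stated background rate, a significant rise would not show that the programme worked. With nobody employed at T0 and 912 followed up, 4 to 6 job-finders suffice, and an assumed background rate of 1% gives significance in 89% to 98% of trials with no programme effect. These figures depend on few participants working at T0, and the size of that group is unknown.

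The cause is the floor together with the uncontrolled design. McNemar's test behaves almost like chi-square when nobody works at T0, so replacing the test is correct but not enough. That the named test is unsuited to change within people is a secondary point, and it matters only if the test is used that way. The argument does not require weight to become the only tested primary outcome. That would be a trade-off for the sponsor, and weight change has no comparator either.

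**What to change.** 1. In Data analysis, state that chi-square tests for independence are used only to compare subgroups, not to test change in employment.
2. Among participants without paid or subsidised work at T0, report the proportion, or cumulative incidence, obtaining first paid or subsidised work by 9 months, with a 95% CI. The hubs already record when work is obtained.
3. Compare that figure with an external job-finding rate fixed in advance, matched as far as possible on area, period and duration of unemployment. If none can be named, label the result descriptive and make no effectiveness claim from it.
4. Report ladder steps 1 and 2 as engagement, and state that step 5 is not evidence separate from reemployment.

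The cost is a change of wording and a desk search for regional statistics, with no new participant data. The employment claim becomes more modest, and any external benchmark will be imperfectly matched to the people who join.
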